# Development of an information system and mobile application for the care of type 2 diabetes patients at the primary care level for the health sector in Mexico: study protocol for a randomized controlled, open-label trial

**DOI:** 10.1186/s13063-022-06177-0

**Published:** 2022-04-04

**Keywords:** Primary care, mHealth, Type 2 diabetes, Control, Treatment compliance, Telemedicine

## Abstract

**Background:**

Providing optimal care for type 2 diabetes (DM2) patients remains a challenge for all healthcare systems. Patients often encounter various barriers in adhering to self-management programs due to lack of knowledge and understanding of self-care activities, lack of individualized and coordinated care, inconvenient and costly education sessions, and poor patient-provider communication. Mobile technologies such as cell phones/smartphones, handheld tablets, and other wireless devices offer new and exciting opportunities for addressing some of these challenges. The purpose of this study is to compare a diabetes management strategy using an information board and a mobile application versus standard care in patients with uncontrolled DM2.

**Method:**

The SANENT (Sistema de Análisis de Enfermedades No Transmisibles) trial is a primary care-based, prospective, two-arm, randomized controlled, open-label, blinded-endpoint study. We aim to recruit 1440 DM2 patients during a period of 6 months until the requested number of participants has been achieved. The total length of the intervention will be 1 year. Both men and women treated for DM2 with an HbA1c > 8.5% and ≥ 20 years of age are eligible to participate in the study. The primary outcome of the study is improved diabetes control measured by changes in HbA1c in the study participants. HbA1c will be measured at baseline, 3-month, 6-month, 9-month, and 12-month follow-up visits in all participants. The main analysis will be based on the intention-to-treat principle. The primary endpoint of the study will be the change in HbA1C within the groups and the differences between the groups. This will be assessed by a repeated measurement approach based on mixed models which contain both fixed effects and random effects.

**Discussion:**

The overall goal of this project is to contribute to the evidence for the use of mobile technology to improve the treatment and regulation of poorly controlled DM2 patients living in Mexico. Our proposed project will show how mobile health technology tools can be used in the treatment of patients with uncontrolled DM2 in primary health care in a Latin American population, and particularly how they could help diabetes patients take better care of themselves.

**Trial registration:**

ClinicalTrials.gov, US National Institutes of Health NCT04974333. Prospectively registered on July 13, 2021. Protocol version number 1, dated August 15th, 2021.

## Background

Type 2 diabetes mellitus (DM2) is one of the fastest-growing public health problems in developed and developing countries and imposes a large financial burden on healthcare systems [1]. The International Diabetes Federation has estimated that the number of adults with diabetes mellitus in Mexico is expected to rise from 12.8 million in 2019 to over 22 million by 2045 of whom more than 95% would have had DM2 [2]. DM2 is a condition that is difficult to treat. Cardiovascular, cerebrovascular, and peripheral vascular diseases are the major complications in patients with DM2 [3]. Moreover, research has shown that patients with DM2 are likely to have a 12–14 years shorter lifespan compared with people without DM2 [4, 5]. Annual health care costs of a patient with DM2 are approximately two to three times higher compared with a person of similar age and sex without diabetes. It has been estimated that approximately 80% of the cost of diabetes to health services in developed countries is spent on complications [6, 7]. With projected increases in the prevalence of diabetes in Mexico and costs arising from the long-term complications incurred by this condition, primary healthcare providers have started to identify self-management interventions that improve diabetes care and patient-related outcomes [8].

Current research has shown that mobile health interventions in patients with DM2 may reduce HbA1c by 0.8% compared with standard care [8–10]. In addition, scientific evidence has revealed a 37% reduction in microvascular complications for each 1% reduction in HbA1c level and an increase in quality-adjusted life years [11–14]. A British study concluded that around 789,000 microvascular and 81,000 macrovascular events could be avoided in the UK among DM2 patients with a 0.8% HbA1c reduction [15].

A recent review showed that the use of mHealth technology in the clinical care of patients with DM2 can result in improved treatment outcomes [16]. They also highlighted that a mHealth intervention need not be restricted to shot messages (SMS) alone. Mobile health technologies have the capacity to grant fast access to information and aid in instant communication for patients with DM2 and healthcare professionals [17]. One third of the current studies were in North America and one third in Asia [18]. Only few studies included DM2 patients in South- America (5%). Moreover, the study setting varied a lot in previous studies with only a 24% of the scientific studies carried out in the primary care sector or specialized outpatient clinics (14%). The mobile health interventions used in previous international studies were also diverse in nature and utilized a wide range of technological innovations such as text messaging (SMS), mobile applications as well as secure websites/web-portals that could be accessed through the diabetes patients' mobile device [8]. Thus, more information is needed on the benefit of mobile health technologies in clinical care settings and whether combining different technological innovations may provide additional benefits.

Therefore, this trial will compare a diabetes management strategy using an information board and a mobile application versus standard care in patients with uncontrolled DM2 within the primary health care system in Mexico.

## Methods

### Trial design

The SANENT (Sistema de Análisis de Enfermedades No Transmisibles [Analysis System for Non -Communicable Diseases]) trial is a primary care-based, prospective, two-arm, randomized controlled, open-label, blinded-endpoint study. This trial aims to recruit 1440 DM2 patients during a period of 6 months until the requested number of participants has been achieved. The total length of the intervention will be one year. The SANENT trial protocol is presented according to Standard Protocol Items: Recommendations for Interventional Trials (SPIRIT) recommendations [19].

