### Sample size calculations

Considering a difference in HbA1c of 1.0% between the intervention and the control group, a standard deviation of 1.5%, a power of 90%, and an alpha of 0.05 (two-sided tests) with a drop-out rate of 25% during the study, a minimum of 126 will be needed in total in each of the three states. As each state where this study will be carried out has a different healthcare provider, we decided to stratify the analysis according to participating state to see whether the intervention works regardless of the healthcare provider. Thus, 126 participants will be recruited in each state. Thus, the total number of patients will be 378. The reason for testing the intervention in each state differently is as the patients belong to different healthcare providers. There may be differences between these systems. We would like to see whether the intervention works within each of the healthcare provider’s systems.

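### The recruitment target is 1440 in the abstract and trial design but 378 in the sample size section, and nothing derives 1440 or says it counts something else

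*Protocol article*

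**What the plan says.** Two places in the protocol article set the target at 1440. The abstract (Method) says "We aim to recruit 1440 DM2 patients during a period of 6 months", and Methods, Trial design, says "This trial aims to recruit 1440 DM2 patients during a period of 6 months until the requested number of participants has been achieved".

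Methods, Sample size calculations, gives another number. From its inputs it concludes that "a minimum of 126 will be needed in total in each of the three states", and then: "Thus, the total number of patients will be 378". It explains that each state has its own healthcare provider and that the aim is to see whether the intervention works within each provider's system.

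The period over which patients are to be recruited also varies. The abstract and Trial design give 6 months. Screening and recruitment gives a 9-month period for enrolment into screening. Trial status gives 20 August 2021 to 12 April 2022.

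**The concern.** Both numbers stand in current text and describe the same three-state, two-arm trial, so they cannot both be the planned enrolment. The Trial design sentence lets accrual run until a requested number is reached, so the end of recruitment depends on which number is meant. In an open-label trial without interim analyses, a single fixed target is a basic safeguard. With two published targets there is a risk that the end point of accrual is ambiguous. The choice also sets how small an effect the trial can detect, how much a null result in one state would mean, and how fast sites must recruit.

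**Working it through.** **Inputs.** From Sample size calculations: "Considering a difference in HbA1c of 1.0% between the intervention and the control group"; "a standard deviation of 1.5" (percentage points); 90% power; two-sided alpha 0.05; "with a drop-out rate of 25% during the study". From Random allocation: 1:1. From Trial setting: three states.

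**Step 1: reproduce the plan's figure.**
- Completers per arm: n = 2 × (1.960 + 1.2816)² × 1.5² / 1.0² = 47.28.
- Both arms: 94.57. Allowing for drop-out: 94.57 / 0.75 = 126.1 per state.
- Three states: 126 × 3 = 378.

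The section is internally consistent. Rounding up to 48 per arm before inflating gives 96 / 0.75 = 128, an immaterial difference.

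**Step 2: compare with 1440.** 1440 / 378 = 3.81. No stated input accounts for this factor. The article gives no split of 1440 by state; an equal split (assumed here) is 480 per state.

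**Step 3: power for a 1.0-point difference.** With n completers per arm after 25% drop-out, power = Φ(1.0 / (1.5 × √(2/n)) − 1.96).

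| Sample | n per arm | Power |
|---|---|---|
| 126, one state | 47.25 | 90.0% |
| 378, pooled | 141.75 | 99.99% |
| 480, one state (assumed) | 180 | over 99.99% |
| 1440, pooled | 540 | essentially 100% |

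The 90% thus belongs to a state of 126 and is the power of neither total.

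**Step 4: difference detectable with 90% power.** This is 3.2415 × 1.5 × √(2/n).

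| | 378 plan | 1440 plan |
|---|---|---|
| Per state | 1.00 (n = 47.25) | 0.51 (n = 180, assumed) |
| Pooled | 0.58 (n = 141.75) | 0.30 (n = 540) |

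For scale, the Background cites an HbA1c effect of 0.8% for mobile health interventions. By the Step 3 formula with 0.8 in place of 1.0, power within a state is about 74% at 126 and about 99.9% at 480.

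**Step 5: monthly accrual under each stated period.**

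| Period | 378 | 1440 |
|---|---|---|
| 6 months | 63 | 240 |
| about 7.7 months (Trial status dates) | 49 | 187 |
| 9 months | 42 | 160 |

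**The case against.** The strongest defence is that no power is lost at the design difference. The 126 is given as a minimum, and both totals reach at least 90% per state for 1.0 point if 1440 splits equally. That stands. A reader might infer from two conflicting sizes that the trial is underpowered, and the calculations do not support that inference.

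A second defence is that 1440 may be the number to be screened. That would mean 378 / 1440 = 26% of those screened being enrolled. The text does not say so: both sentences speak of recruiting patients, Trial design ties the figure to the requested number of participants, and screening is described separately. If screening was meant, the wording still has to change.

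A third point is that the figures in Step 4 are approximations. They treat the analysis as a simple two-sample comparison, whereas the article plans a repeated-measures mixed model with covariates and analysis by state. This is correct, and they should be read only as showing the scale of the gap.

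Two further inferences go beyond the documents. One is that 378 must be the right number because it alone has a derivation; a derivation shows which number is explained, not which was approved. The other is that the investigators intend to stop recruitment at their discretion. Nothing suggests this, and interim analyses are ruled out; ambiguity about when accrual ends is a risk only.

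**Conclusion.** The contradiction holds and should be corrected before the planned size is relied on. The article states two enrolment targets that differ 3.8-fold (1062 patients), and only 378 is derived. The defect is an undefined target, with 1440 unjustified. The arithmetic of the sample size section is sound.

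The practical consequence is sensitivity to effects below 1.0 point: roughly 1.00 versus 0.51 per state and 0.58 versus 0.30 pooled. Required accrual is 42 to 63 per month for 378, against 160 to 240 for 1440, depending on which stated period applies. These figures rest on SD 1.5, 25% drop-out and a two-sample comparison. The per-state figure for 1440 also rests on an assumed equal split of 480.

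**What to change.** Confirm which target was approved, and give that single number in the abstract, in Trial design (including the sentence on how long accrual runs) and in Sample size calculations.

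- If it is 378, replace 1440 in the abstract and Trial design.
- If it is 1440, replace the present calculation with one that yields 1440, give the split by state, and restate power and detectable difference per state and pooled.
- If 1440 is the number to be screened, say so and give the enrolment target beside it.

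This costs a wording correction if sites already work to the approved number. If they work to the other one, the gap is 1440 − 378 = 1062 patients and the correction becomes operational.

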### Trial setting

This trial will be conducted within primary health care practices in three states (Colima, Tlaxcala, and Guanajuato) of Mexico. These states were selected because they are some states with a high prevalence of diabetes in México [20–22] and have implemented an Electronic Health Record System.

### Patient and public involvement

During the planning phase of the study, a pilot project was carried out evaluating the design and applicability of the information board and mobile application in 31 DM2 patients. The final intervention was then modified according to the qualitative data received from the patients. We also involved primary healthcare clinicians in the development and evaluation of the information. The results of the study will be made available to all trial participants and participating general practices.

### Sample size calculations

Considering a difference in HbA1c of 1.0% between the intervention and the control group, a standard deviation of 1.5%, a power of 90%, and an alpha of 0.05 (two-sided tests) with a drop-out rate of 25% during the study, a minimum of 126 will be needed in total in each of the three states. As each state where this study will be carried out has a different healthcare provider, we decided to stratify the analysis according to participating state to see whether the intervention works regardless of the healthcare provider. Thus, 126 participants will be recruited in each state. Thus, the total number of patients will be 378. The reason for testing the intervention in each state differently is as the patients belong to different healthcare providers. There may be differences between these systems. We would like to see whether the intervention works within each of the healthcare provider’s systems.

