#### Primary and secondary endpoint analysis

The primary endpoint of the study will be the change in HbA1c between the intervention and the control group. This will be assessed by a repeated measurement approach based on mixed models which contain both fixed effects and random effects. These models are likelihood-based approaches in the presence of non-ignorable missing data (e.g., missing at random). the main purpose will be to determine whether the within-person changes over time vary across levels of one or more between-person factors (e.g., blood pressure measurement technique and for the same covariates included in the model for coprimary endpoints). Exploratory analysis will consist of profile graphs and Pearson’s correlation matrix. The Mauchly test will be applied to verify the fulfillment of the Huynh-Feldt condition. A mixed linear model will be used. To select the most appropriate covariance matrix, the Alkaike AIC or the Swartz BIC criteria will be used. The models will be controlled for age, sex, and time with the diagnosis of diabetes. No subgroup analysis will be conducted. Also, interim analyses will not be performed in this study.

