Typical use of mobile health technologies for the treatment of diabetes has been focused on mobile and web-based applications [32–46]. A recent review of 15 systematic reviews summarized that mobile health technologies interventions improve glycemic control (HbA1c) compared with standard care or other approaches by as much as 0.8% for patients with DM2 and 0.3% for patients with DM1, at least in the short-term (< 12 months) [8]. One of the very few studies using mobile health technologies conducted among the Hispanic population revealed that the use of a simple, low-cost text-messaging (up to three motivational, educational, and/or call-to-action text messages per day over 6 months) program was highly acceptable in a sample of high-risk, Hispanic DM2 patients in Texas and led to greater improvement in glycemic control compared with usual care [47]. None of the previous work has combined educational strategies with mobile technologies to improve treatment compliance and self-management. Latin American DM2 patients have specific needs, and this should be reflected in diabetes mobile health applications designed for this population. Existing research suggests that many Latin American DM2 patients do not possess sufficient diabetes knowledge or self-awareness to fully benefit from the most prevalent functionalities offered by the most popular diabetes mobile applications [47]. Therefore, it has been recommended that developers incorporate more basic features such as diabetes education, reminders to check blood glucose levels or to take medications, Spanish language interfaces, and glucometer connectivity, which are relatively underrepresented in the most popular diabetes applications currently available in Spanish. The mobile tools that have been developed for this project incorporate all these components to achieve the objectives. The main innovation of this prosed project is that we are interested in showing how mobile health technologies can improve motivation in a primary health care setting in a Latin American population of a middle-income country and particularly how these strategies could help patients take better care of themselves and help patients to take better decisions about the management of their health condition.

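### The sample size is built on a separate comparison in each state, but the analysis section describes one overall model without a state term and rules out subgroup analysis

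*Protocol article*

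**What the plan says.** All references are to the protocol article.

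- **Sample size calculations.** The inputs are a 1.0-point HbA1c difference, SD 1.5, 90% power, two-sided alpha 0.05 and 25% drop-out. They lead to 126 patients per state and 378 over three states. The reason given for sizing by state is that the providers differ between states: "we decided to stratify the analysis according to participating state to see whether the intervention works regardless of the healthcare provider". The section adds that the investigators want to know whether the intervention works inside each provider's system.
- **Primary and secondary endpoint analysis.** The primary endpoint is one comparison of HbA1c change between the two arms, by a mixed model for repeated measurements. On covariates: "The models will be controlled for age, sex, and time with the diagnosis of diabetes". State and site are not named, and neither is a treatment-by-state term. The section then says: "No subgroup analysis will be conducted".
- **Random allocation.** Allocation is balanced on study site, age, sex, diabetes duration and number of medications. Site and number of medications do not appear in the covariate list.

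**The concern.** The two sections describe different trials. One is three state trials run side by side, each with its own test. The other is a single trial with one pooled result and no look by state. An analyst who follows the analysis section drops the question that determined the sample size. An analyst who follows the sample size section appears to break the subgroup ban.

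Nor does the article say what would count as success if three state tests were run. A split result, with one or two states significant, would have no agreed meaning, and a chance split could be read as a real difference between providers. The stated 90% does not measure the aim of showing benefit regardless of provider.

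**Working it through.** **Inputs** (Sample size calculations, except the last)

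- Difference: "Considering a difference in HbA1c of 1.0% between the intervention and the control group"
- SD: "a standard deviation of 1.5" percentage points
- Alpha: "an alpha of 0.05 (two-sided tests"), with no adjustment for three tests mentioned
- Power 90%
- Drop-out: "with a drop-out rate of 25% during the study"
- Allocation 1:1 (Random allocation)

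**1. Reproduce 126.** Per arm, n = 2 × (1.960 + 1.282)² × 1.5² / 1.0² = 47.3. Both arms: 94.6. Divided by 0.75: 126.1. Rounding up to 48 per arm first gives 96 / 0.75 = 128. The stated 126 is reproduced, and 3 × 126 = 378. So 90% belongs to one two-arm test in one state.

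**2. Power in one state.** 126 × 0.75 / 2 = 47.25 completers per arm. The standard error of the difference is 1.5 × √(2/47.25) = 0.309. Power = Φ(1.0/0.309 − 1.960) = Φ(1.280) = 0.900; with the t-test, 0.894.

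**3. Power in all three states.** Assuming independent states and a true difference of 1.0 in each:

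- nominal: 0.90³ = 0.729
- t-test: 0.894³ = 0.714

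For 90% in all three, each state needs 0.90^(1/3) = 0.965. That is 65 per arm, 130 completers, 130/0.75 = 174 per state and 522 in total.

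**4. Type I error if any one state counts.** 1 − 0.95³ = 0.143.

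**5. Power of the pooled test.** 378 × 0.75 / 2 = 141.75 completers per arm. The standard error is 1.5 × √(2/141.75) = 0.178. Power at 1.0 is over 99.9%. The difference detectable with 90% power is 3.242 × 0.178 = 0.58. So 378 is not the size one would derive for the single comparison in the analysis section.

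**6. How often the states would split.** With the t-test powers and the same true effect in every state:

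| True difference | Power per state | All three | Exactly two | Exactly one |
|---|---|---|---|---|
| 1.0 | 0.894 | 71% | 25% | 3% |
| 0.8 | 0.728 | 39% | 43% | 16% |

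The 0.8 row is a sensitivity case. It is the size the Discussion reports for mobile health interventions, "compared with standard care or other approaches by as much as 0.8% for patients with DM2". Whether 1.0 was a sound planning value is a separate matter.

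**7. Power to detect provider differences.** The contrast between two state effects has standard error 0.309 × √2 = 0.436, so 80% power needs a gap of (1.960 + 0.842) × 0.436 = 1.2 points. With true effects of 1.0, 1.0 and 0, the noncentrality is 0.667/0.0952 = 7.0, and the 2-df interaction test has about 66% power.

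**The case against.** The strongest defence is that the two sections can be read together: fit the stated model separately in each state, so that no state term is needed, and take the ban to mean subgroups other than the planned strata. That reading is possible, so it would go too far to say that the sections cannot both be followed. But the analysis section does not say it. It describes one overall comparison, and its ban has no exception. A separate statistical analysis plan may hold more detail, but it would still have to depart from one of the two statements published here.

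Several stronger readings are tempting and are not supported:

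- **That the protocol claims 90% power for all three states jointly.** It does not; it attaches 90% to each state's number. The point is only that this figure does not answer the stated aim.
- **That type I error is inflated to 14.3%.** This holds only under an any-state rule, which the article never states. If all three states must succeed, no adjustment is needed.
- **That one significant state out of three is the likely outcome.** At 1.0 it has 3% probability and at 0.8 it has 16%.
- **That leaving out state biases the result.** Allocation is randomised and balanced on site, so the omission mainly costs precision.
- **That a pooled primary test is the only acceptable repair.** Keeping the by-state tests, with a stated success rule, is equally legitimate.

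The figures also assume 378. The Abstract and the Trial design section give 1440. If that number were recruited equally (480 per state, an assumption), power in all three states would be over 99.9% at 1.0. Power would then not be the difficulty, but the mismatch between the sections would remain.

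**Conclusion.** The point stands as an inconsistency between the sample size section and the analysis section. The arithmetic behind 126 is sound. What is wrong is that the analysis, followed as written, neither adjusts for nor examines the provider differences for which the trial was sized, and that no rule says how three state results would be read.

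The size of the gap at 378 is 90% power in one state against about 71–73% for success in all three. This rests on SD 1.5, 25% drop-out, independent states and a true difference of 1.0 in each. The mismatch itself does not depend on these assumptions. It should be settled before any unblinded data are seen, because it decides which test is the trial's primary result.

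**What to change.** 1. Reconcile the two sections. Put state in the primary model, together with the other allocation factors.
2. Pre-specify the treatment-by-state term, with state-specific estimates and confidence intervals, and amend the subgroup sentence so that analysis by state is exempt.
3. State which test is primary:
   - **Pooled:** one state-adjusted comparison at two-sided 0.05, with the state results supportive and the low power of the interaction test acknowledged; or
   - **By state:** three tests with a stated success rule, either all three at 0.05 or any state with control of alpha.
4. Restate the power to match: over 99.9% for the pooled test at 1.0, or 90% per state and about 71–73% for all three. If 90% for all three is wanted, the size is 522.
5. Reconcile 378 with 1440 separately, and recompute these figures if the target changes.

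Items 1 to 4 cost only protocol or analysis plan wording, with the same patients and data, unless 522 is chosen. The pooled option has a real price: the per-provider question becomes supportive rather than confirmatory. The all-three option keeps that question at the lower power shown.
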